### Outcomes {12}

#### Primary outcome measure

An *incisional hernia* at the ileostomy closure site within 2 years of follow-up represents an outcome with the highest long-term impact for the patient and the healthcare system and is therefore selected as the primary endpoint. The duration of follow-up (2 years) is recommended by the EHS as the rate of IH increases after 1 year [25]. Furthermore, the primary endpoint is recommended by the EHS as it is clearly measurable and reproducible. Consequently, “any abdominal wall gap with or without a bulge in the area of a postoperative scar perceptible or palpable by clinical examination or imaging” is regarded as an IH*.*

Patients will be assessed for the primary endpoint at 12 and 24 months after the trial intervention. At these dates, patients will be examined by a clinician blinded for the trial intervention and by a radiologic examination performed by a blinded assessor. Radiologic exams allowed for assessment in the trial are for example sonography, computed tomography (CT) or magnetic resonance imaging (MRI) scans. To reduce radiation exposure, sonography is the preferred imaging method. No radiation-associated imaging should be initiated solely for the purpose of the P.E.L.I.O.N trial. However, results of radiation-associated imaging like CT scans that are performed for other indications (e.g. oncological follow-up) can be used in the trial. In this case, an additional ultrasound of the abdominal wall is not necessary. In case of conflicting results between clinical and radiologic exams, the radiologic imaging is decisive to increase sensitivity [25]. If only one of the two examinations is performed (i.e. either clinical or imaging), the result of this assessment will be used for analysis. As many patients included in this trial are expected to have an oncological indication and the included centres perform their oncological follow-up themselves, the loss to follow-up of patients is expected to be low. Possible results of the primary outcome assessment are listed in Table 2.

**Table 2 Tab2:** Possible outcomes of clinical and radiological hernia assessment and outcome decisions in the P.E.L.I.O.N. trial

Clinical exam result	Imaging result	Primary endpoint
**Hernia**	Hernia	**Hernia**
**No hernia**	Hernia	**Hernia**
**Hernia**	No hernia	No hernia
**No hernia**	No hernia	No hernia
**Hernia**	Missing	**Hernia**
**No hernia**	Missing	No hernia
**Missing**	Hernia	**Hernia**
**Missing**	No hernia	No hernia

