
For patients who are unable or unwilling to attend the follow-up visits, a telephone follow-up is incorporated. As the patient-reported outcome questionnaire developed by Tastaldi et al. (Hernia Recurrence Inventory, HRI) was modified and will be used in all patients [26], it can be used as a screening tool during telephone visits, i.e. patients who are suspected to have an IH based on the questionnaire might be convinced to attend an outpatient visit, even if they were reluctant to do so before. Time-to-event analyses for the primary endpoint are not justified as it is highly dependent on the density of the follow-up schedule and clinical symptoms and our interest is whether a hernia occurs rather than when a hernia occurs.

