#### Secondary outcome measures

Postoperative complications within 30 days according to the Dindo-Clavien classification (DCC) ≥3 [27]Number of surgical site occurrences (SSO) [28] defined as the sum of the following *individual* secondary endpoints:*Superficial or deep surgical site infections* (SSIs) within 1 year after index operation according to the CDC definition [29]. Follow-up for this endpoint will be 1 year as defined by the CDC in case of foreign body placement [29]. Organ-space SSIs are excluded in this measurement as they are independent of the abdominal wall closure technique, but rather depend on the underlying surgery. Furthermore, they are infrequent after ileostomy reversal. In addition, clinically relevant organ-space SSIs (defined as Dindo-Clavien ≥ grade 3) will be recorded in the overall complication rate according within 30 daysRate of *wound seromas* at former ostomy site within 30 days after index operation. Seroma will be defined as a collection of serous fluid in a dead space, which can either be in situ or leaking through a wound [30]. Assessment can be by clinical or radiologic examinationRate of *wound hematomas* at former ostomy site within 30 days after index operation. Hematomas are defined as an accumulation of blood in the wound area, which warrants (bedside) surgical exploration and intervention [31]*Enterocutaneous fistulas* within 24 months after index operation [28]Number of patients undergoing *incisional hernia repair* at the site of ileostomy closure within 24 months after the index operationNumber of *revision surgeries* because of complications related to ileostomy closure within 24 months after the index operation*Chronic postoperative pain* in the ileostomy closure site during follow-up measured via the Pain Questions of the modified EHS-QoL questionnaire at 12 and 24 months [32]*Health-related quality of life* at baseline, 12 and 24 months after index operation according to the EHS-QoL questionnaire [32]*Modified Hernia Recurrence Inventory (HRI)* at 12 and 24 months [26]

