### Participant timeline {13}

Patients scheduled for elective loop ileostomy closure are screened preoperatively (visit 1) (Fig. 1). Patients are enrolled given their ability to understand the extent and nature of the trial as well as their written informed consent after detailed patient information. All inclusion criteria and no exclusion criteria must be fulfilled. Baseline data are collected during screening/baseline visit. Included patients are randomised during surgery (visit 2). The ostomy closure will be performed as randomised. Follow-up visits will be on postoperative days 2–4, at discharge and on days 30–35 (visits 3–5) for evaluation of secondary endpoints. In addition, 12 and 24 months (visits 6–7) after surgery patients are planned for follow-up to evaluate primary and secondary outcome parameters. In case the patient is unable to attend clinical visits 6–7, a telephone evaluation will be performed. If the interview reveals a strong indication for the presence of an incisional hernia, the patient will be once again asked to present to the outpatient clinic for clinical and ultrasound evaluation. Protocol deviations will be assessed during the entire study period. An overview of the trial visits and collected data can be found in Table 3.

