The IH rates will be compared via a mixed logistic regression model including the factors treatment group and IH risk (high vs. low) as fixed effects and centre as a random effect. As the number of centres is relatively large in relation to the sample size, inclusion of the centre as a random effect instead of a fixed effect is indicated. Differences between centres cannot be ruled out but are of no special interest in the primary analysis; inclusion of centre as the random effect is recommended [38]. Besides this, the interpretation is more straightforward because “[…] in the context of RCTs, centre effects can be regarded as a nuisance parameter, as the primary goal is to estimate the treatment effect”. For the structure of the covariance matrix of the random intercept of centre, a variance component structure is used allowing for different variability within each centre while assuming that centres are independent. Missing data for the primary outcome variable due to dropout or loss to follow-up are assumed to be at least “missing at random” and will be replaced by using multiple imputation. Occurrence of IH after the ICE re-laparotomy affecting the loop ileostomy closure site and death without prior observation of IH will be imputed the same way. Information whether a patient was event-free regarding the occurrence of an IH before loss-to-follow-up, dropout or the respective ICEs will be included into the multiple imputation procedure. This will be done by imputing the primary endpoint “incisional hernia within 24 months” (yes/no) using the variable “incisional hernia within 12 months” (yes/no) besides treatment group, IH risk (high vs. low) and centre using the fully conditional specification (FCS) and the discriminant function method. ICEs that are handled using a treatment policy strategy will be ignored in the primary analysis. The proportion of each ICE will be described by group to support the interpretation of the primary effect estimate.

Sensitivity analyses regarding the imputation method and the underlying assumptions will be performed. These include applying a pattern mixture model under the assumption of a “missing not at random” data mechanism, as well as best- and worst-case scenarios to assess the robustness of the results.

Within a sensitivity analysis, oncologic treatment will be included into the logistic regression model for the primary endpoint as an additional covariate.

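### The imputation model for 24-month hernia omits the Hernia Recurrence Inventory, although telephone non-attenders are recalled selectively on suspicion of hernia; the effect is modest and falls on the arm rates and risk difference

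*Protocol article*

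**What the plan says.** Three parts of the protocol article bear on each other.

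- **Imputation.** Under Statistical methods {20a}, missing primary outcomes "are assumed to be at least “missing at random” and will be replaced by using multiple imputation". The endpoint is imputed "using the variable “incisional hernia within 12 months” (yes/no") "besides treatment group, IH risk (high vs. low) and centre using the fully conditional specification (FCS"), with the discriminant function method. The HRI is not among the listed variables.
- **Telephone follow-up.** Under Participant timeline {13}, patients who cannot attend the 12- or 24-month visit are evaluated by telephone. "If the interview reveals a strong indication for the presence of an incisional hernia, the patient will be once again asked to present" to the clinic. Under Primary outcome measure, the HRI "was modified and will be used in all patients" and may be used as a screening tool at telephone visits: "patients who are suspected to have an IH based on the questionnaire might be convinced to attend an outpatient visit". Secondary outcome measures and Table 3 schedule it at 12 and 24 months.
- **What counts as an endpoint.** "If only one of the two examinations is performed (i.e. either clinical or imaging), the result of this assessment will be used for analysis". Table 2 recognises only clinical and imaging results, so a telephone interview without an examination leaves the endpoint missing.

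**The concern.** Missing at random is a statement about the variables in the imputation model. Among patients reached only by telephone, a suspicious interview can turn a missing endpoint into an observed one, while a reassuring interview leaves it missing. Missingness in that subset thus depends on HRI-informed answers, which also predict hernia. Given only 12-month IH, treatment, IH risk and centre, the patients who stay missing have fewer hernias than the observed patients from whom they are imputed.

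Both arm rates are then too high, and the arm with more hernias gains more percentage points. That matters because the estimand's summary measure is the difference in IH rates. The 12-month variable removes only part of the problem: recall at 24 months responds to symptoms that arise after month 12.

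**Working it through.** **The plan's own figure.** With 30% vs 15%, two-sided 5% and 80% power, pooled variance without continuity correction:

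n = [1.960·√(2·0.225·0.775) + 0.8416·√(0.30·0.70 + 0.15·0.85)]² / 0.15² = 120.5, so 121 per group. Then 121/0.80 = 151.25, so 152 per group and 304 in total. The stated sample size reproduces and is not affected by this point.

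**Inputs.** The 30% and 15% come from Sample size {14}. Everything else is an assumption, because the document gives no figures for it:
- IH by 12 months of 20% (control) and 10% (mesh), known for everyone
- m, the share reachable only by telephone at 24 months, unrelated to hernia: 0.2–0.3
- HRI sensitivity se and specificity sp, equal in both arms: 0.8–0.9
- q, the share of HRI-positive telephone patients who then attend: 0.5–1; HRI-negatives stay missing

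**Formulas.** A patient with IH at 12 months already has the endpoint, so only those hernia-free at 12 months need imputing. Among them:
- true later risk p = (P24 − P12)/(1 − P12)
- HRI-positive share pos = p·se + (1 − p)(1 − sp)
- observed rate r = [(1 − m)p + m·q·p·se] / [(1 − m) + m·q·pos]
- true rate in those still missing = (p − q·p·se)/(1 − q·pos)
- estimated arm rate = P12 + (1 − P12)·r, because the missing are imputed at r

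**Example: m = 0.2, se = sp = 0.8, q = 0.5.**
- Control: p = 0.10/0.80 = 0.125; pos = 0.275; r = (0.100 + 0.010)/(0.800 + 0.0275) = 0.1329. True rate in the missing = 0.075/0.8625 = 0.0870. Estimated rate = 0.20 + 0.80·0.1329 = 30.6%.
- Mesh: p = 0.05/0.90 = 0.0556; pos = 0.2333; r = 0.04889/0.82333 = 0.0594. True rate in the missing = 0.0377. Estimated rate = 0.10 + 0.90·0.0594 = 15.3%.
- Difference 15.3 points against a true 15.0.

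**Four scenarios with 12-month IH in the model:**

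| m | se = sp | q | Control | Mesh | Difference (points) | Odds ratio |
|---|---|---|---|---|---|---|
| 0.2 | 0.8 | 0.5 | 30.6% | 15.3% | 15.3 | 0.410 |
| 0.2 | 0.8 | 1.0 | 31.2% | 15.7% | 15.6 | 0.409 |
| 0.2 | 0.9 | 0.8 | 31.3% | 15.7% | 15.6 | 0.409 |
| 0.3 | 0.9 | 1.0 | 32.8% | 16.5% | 16.2 | 0.406 |
| True values | | | 30.0% | 15.0% | 15.0 | 0.412 |

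A simulation with 4 million patients per arm gave the same figures to within about 0.1 points.

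**With the HRI added.** In the example's control arm, the rate is 0.100/0.275 = 0.3636 among HRI-positives and 0.025/0.725 = 0.0345 among HRI-negatives. The missing are 0.2·0.725 = 0.145 HRI-negative and 0.2·0.5·0.275 = 0.0275 HRI-positive. Their imputed rate is (0.145·0.0345 + 0.0275·0.3636)/0.1725 = 0.0870, the true value. The simulation recovered about 30.0% and 15.0% in all four scenarios.

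**Why the odds ratio holds.** Leave out the 12-month variable for a moment. The chance of being observed is (1 − m) + m·q·se with hernia and (1 − m) + m·q·(1 − sp) without, the same pair in both arms. In the example these are 0.88 and 0.82. Both arms' odds are multiplied by 0.88/0.82, so the odds ratio stays exactly 0.412. With the 12-month variable it shifts only to the values in the table. If both arms have the same true rates and the same recall, both are inflated equally and the difference is zero.

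**The case against.** The strongest counter-argument is that the primary comparison is a mixed logistic regression, and the odds ratio hardly responds to this kind of selection. That stands. A reader might infer that the confirmatory test is tilted towards mesh. The documents do not support this: there is no bias under the null with equal recall. The movement towards mesh is on the risk-difference scale, while the relative risk moves slightly the other way (0.500 to 0.501–0.504 in the four scenarios).

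A reader might also compute a larger effect by ignoring 12-month status. With 15–30% initial non-attendance, HRI accuracy of 70–90% and 50–80% recall, the difference then ranges over 15.3–16.9 points. The plan does use 12-month IH, so that range overstates the problem.

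Nor does the protocol set an HRI score or cut-off that decides who is recalled. It says the questionnaire can be used for screening and speaks of a strong indication at interview. The dependence is on a judgement informed by the HRI, which is enough for the point but weaker than a formal rule.

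The telephone-only share is probably generous too. The 20% allowance in the sample size section also covers dropouts and intercurrent events, including death. Patients who died, withdrew or were not reached are not subject to this recall. Imaging done for other reasons can supply the endpoint, and the protocol expects low loss.

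Finally, a pattern mixture model, best- and worst-case scenarios and a complete case analysis are planned. They probe the assumption but are not stated to use the HRI, and they do not correct the primary estimate.

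**Conclusion.** The point holds as a modest flaw in the stated imputation model. The article gives an explicit predictor list, which omits a scheduled variable that informs recall. For patients reached only by telephone, missing at random therefore does not hold given that list.

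Under the assumptions above, the arm rates are inflated by about 0.3–2.8 points and the risk difference by about 0.3–1.2 points. For scale, the standard error of the difference is √(0.3375/152) = 4.7 points at 152 per group and √(0.3375/121) = 5.3 at 121. The distortion is well below sampling error and does not threaten the test of the null hypothesis. It is worth correcting because the rate difference is the declared summary measure and the data needed are already scheduled.

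The size rests on assumed values for telephone-only follow-up, HRI accuracy, recall and 12-month rates, and on equal HRI accuracy and recall in the two arms.

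**What to change.** Add the modified HRI results at 12 and 24 months, from visit or telephone, as auxiliary variables in the fully conditional specification model for the primary endpoint. Documented hernia repair at the closure site is an optional further predictor. As a supplement to the planned sensitivity analyses, add one that counts HRI-negative telephone-only patients as hernia-free.

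The cost is a change of wording and one or two more variables in the imputation call. These variables will themselves be missing for patients who were not reached, so they too must be imputed. No new data, visits or patients are needed. The protocol has the analysis plan finished before database closure by a blinded statistician, so the change can be prespecified there.

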### Sample size {14}

Sample size calculation is based on the rate of the primary endpoint (IH rate) within 24 months after surgery. Based on the assumption that the percentage of patients developing an IH in the control group is 30% (4–7), we hypothesise a reduction to 15% in the intervention arm (conservative reduction rate below that reported in the above-mentioned trials). Consequently, a sample size per group of 121 patients is needed for the group comparison by the chi-squared test to achieve 80% power in detecting this difference in IH rate at a two-sided level of significance of 5%. It is assumed that using a logistic regression model adjusting for IH risk (low-risk vs. high-risk patients: BMI ≥ 27) and including centre as a random effect in the primary analysis will lead to less unexplained variance and thus to an increased power.

The intercurrent event re-laparotomy affecting the loop ileostomy closure site and death without prior observation of IH are expected to be very rare, with just a few patients each. Based on previous trials, to account for the loss of information, a rate of 20% of dropouts, loss to FU and relevant ICEs (handled with the hypothetical strategy) is considered. Therefore, a total of 304 patients (152 per group) will be randomised. The other ICEs are ignored in the primary estimand and not accounted for in the sample size calculation. Calculation was performed using PASS 16.0.12. Only high-volume trial sites committing to include at least 10 patients per year will be chosen as trial sites.

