### Methods for additional analyses (e.g. subgroup analyses) {20b}

Pre-specified subgroup analysis will be performed in the FAS population for the rate of IH in the following subgroups: (a) body mass index (< 27 vs. ≥ 27), (b) neoadjuvant therapy (yes/no), (c) COPD vs. non-COPD, (d) previous laparotomy vs. previous minimal invasive surgery and (e) history of hernia/hernia repair vs. no history of hernia/hernia repair.

Furthermore, uni- and multivariate analyses using two-level binary logistic regression models will be performed to find risk factors for IH. Factors that will be included in the model (besides the fixed factors treatment group and IH risk, and the random factor centre which are already used in the primary model) are age, BMI, sex, presence/absence of diabetes mellitus with chronic complications, corticosteroid use, preoperative (radio)chemotherapy, renal disease, smoking, previous laparotomies, COPD, cardiovascular disease, history of hernia or hernia repair, history of abdominal aortic aneurysm, ASA classification, occurrence of SSI, postoperative complication (Dindo-Clavien), seroma formation, hematoma formation and length of hospital stay.

Furthermore, the treatment effect will be assessed descriptively within several subgroups of interest to identify potential prognostic and predictive factors.

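### The listed imputation model omits four of the five subgroup factors, oncologic treatment and every treatment-by-factor term; reusing its imputations in the secondary analyses would pull their estimates toward the average (minor)

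*Protocol article*

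**What the plan says.** Section {20a} of the protocol article fixes the imputation model for the primary endpoint. Hernia within 24 months is imputed from hernia within 12 months "besides treatment group, IH risk (high vs. low) and centre using the fully conditional specification (FCS) and the discriminant function method". No interaction with treatment is listed. The Sample size section {14} defines IH risk by BMI at or above 27.

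Three further analyses of the same endpoint use factors outside that list:

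- **Subgroups, section {20b}.** "Pre-specified subgroup analysis will be performed in the FAS population for the rate of IH in the following subgroups": BMI at 27, neoadjuvant therapy, COPD, open versus minimally invasive previous surgery, and hernia history. The full analysis set is all randomised patients ({20a}). How missing outcomes are treated in these analyses is not stated.
- **Oncologic sensitivity model, section {20a}.** Here "oncologic treatment will be included into the logistic regression model for the primary endpoint as an additional covariate".
- **Risk-factor regression, section {20b}.** It keeps treatment, IH risk and centre from the primary model and adds 19 candidate factors.

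Section {20a} also plans a complete-case analysis of the primary endpoint in the full analysis set. Section {20c} does not settle the question for the subgroups.

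**The concern.** An imputation model should contain whatever the later analysis estimates. If a factor and its interaction with treatment are left out, patients with imputed outcomes receive the average mesh effect, whichever subgroup they belong to. Mixing them with observed patients dilutes the subgroup contrast, and Rubin's rules cannot undo this because the dilution is in the imputed values. A factor omitted as a main effect has its own coefficient diluted in the same way.

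At stake is the description of who benefits from mesh and which factors predict hernia. The direction is systematic: the subgroups look more alike than they are. For oncologic treatment, the dilution favours the plan's own assumption that systemic therapy is unlikely to affect the endpoint.

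**Working it through.** **1. The plan's own figure.** "a sample size per group of 121 patients is needed for the group comparison by the chi-squared test to achieve 80% power", for 30% versus 15% at two-sided 5%. With pooled variance and no continuity correction:

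n = [1.96·√(2·0.225·0.775) + 0.8416·√(0.30·0.70 + 0.15·0.85)]² / 0.15² = 120.5, so 121 per group.

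Then 121/0.80 = 151.25, so 152 per group and 304 in total. This reproduces the plan. For loss, the plan states that "a rate of 20% of dropouts, loss to FU and relevant ICEs (handled with the hypothetical strategy) is considered". So 20% is the planned share of unknown or imputed outcomes.

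**2. Which factors are in the imputation model**

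| Factor | Main effect | Treatment interaction |
|---|---|---|
| BMI at 27 | yes, as IH risk | no |
| Neoadjuvant therapy | no | no |
| COPD | no | no |
| Open vs minimally invasive previous surgery | no | no |
| Hernia history | no | no |
| Oncologic treatment (covariate only) | no | not needed |

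**3. Dilution of a subgroup contrast if the imputations are reused.** Assumed, not in the document: control rate 30% in both subgroups, mesh rates 5% and 25%, equal subgroups. The true difference between the two risk differences is then 0.20, and the overall effect is the planned 15 points. Two-thirds of hernias are taken as present by month 12 in both arms; the background section gives about 20% at 12 months, against the assumed 30% at 24.

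Let m be the share lost, λ the part of losses after month 12, and f = 2/3. A patient lost early carries no subgroup information; one lost late has lost only the second-year part:

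shrinkage ≈ m·[(1 − λ) + λ(1 − f)]

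Simulation: N = 304, 3,000 replicates, 10 imputations, simulation error about 0.0016 to 0.0019.

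| Loss | Timing | Formula | Simulated, factor omitted | Simulated, factor and interaction included |
|---|---|---|---|---|
| 20% | all before month 12 | 0.160 | 0.159 | 0.202 |
| 20% | half | 0.173 | 0.169 | 0.200 |
| 20% | all after | 0.187 | 0.187 | 0.202 |
| 10% | all before month 12 | 0.180 | 0.182 | 0.200 |
| 10% | half | 0.187 | 0.186 | 0.202 |
| 10% | all after | 0.193 | 0.193 | 0.199 |

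By the formula, shrinkage is 7-20% at 20% loss and 3-10% at 10% loss. The overall risk difference stayed at about −0.15 in every run.

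**4. Against sampling error.** With 76 patients per cell, the standard error of the contrast is √(2·0.30·0.70/76 + 0.05·0.95/76 + 0.25·0.75/76) = 0.093. At 25% prevalence it is 0.113. The largest shift is 0.041, and 0.041/0.093 = 0.44.

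**5. False benefit in a subgroup with none.** Suppose equal subgroups, 30% to 10% in one and 30% to 30% in the other. The average effect is 10 points, so the no-effect subgroup shows about 0.067 × 10 = 0.7 to 0.20 × 10 = 2.0 points of benefit.

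**6. Oncologic covariate.** Assume an odds ratio of 2, 50% prevalence, 20% imputed and no 12-month information. The covariate log odds ratio falls from 0.69 to 0.55. The treatment log odds ratio moves from −0.887 to −0.881.

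**7. Price of the fix.** At 20% loss, the replicate standard deviation of the contrast rises from 0.085 to 0.105 (all early losses) or from 0.090 to 0.100 (all late).

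**The case against.** The strongest objection is to the premise. A reader might infer from the full analysis set that the subgroup analyses use the imputed outcomes. The document does not say so. That set is defined by who is included and in which group, and section {20a} itself plans a complete-case analysis within it. This stands: for the subgroups, reuse is an inference. It is the natural reading for the other two models, because one adds a covariate to the primary endpoint's regression and the other extends terms already in the primary model.

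It can also be said that handling missing data in secondary analyses belongs in the statistical analysis plan, which is not shown. That is fair as far as silence goes. But the article does fix the list of predictors, and as listed it does not suit these analyses.

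Other points stand:

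- BMI is in the model through IH risk; only its treatment interaction is missing.
- The oncologic model estimates no subgroup difference, and its treatment effect hardly moves.
- The plan expects low loss to follow-up, so 20% is an allowance rather than a forecast.
- Section {20b} calls the assessment of treatment effects within subgroups descriptive.
- The fix does not gain precision. With all losses early, root mean squared error is √(0.041² + 0.085²) = 0.094 with the factor omitted and √(0.002² + 0.105²) = 0.105 with it included. The case for changing rests on removing a one-directional bias.

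**Conclusion.** The point holds as a minor one. The listed imputation model does not match the planned subgroup, oncologic-covariate and risk-factor analyses. Reusing its imputations would shrink subgroup contrasts by about 7-20% at the planned 20% loss, and would dilute the coefficients of omitted factors. The shift is below half a standard error.

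This rests on assumed subgroup rates, prevalences and timing of losses, an assumed covariate odds ratio, and the two-thirds share by month 12 in both arms. It also rests on reuse of the imputations, which the document implies for two of the analyses but does not state for the subgroups.

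Two stronger readings are not supported. One is that the primary result is at risk: the overall effect was unchanged in every run. The other is that a subgroup without benefit would show a material false one: under the equal-subgroup assumptions above it is at most about 2 points.

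**What to change.** Keep the primary imputation and the confirmatory test as they are. State for each of the three secondary analyses whether imputed outcomes are used. Where they are:

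- **Subgroups:** for each analysis, re-impute with that one factor and its treatment interaction added. For BMI only the interaction is new.
- **Oncologic and risk-factor models:** add the analysed covariates to the imputation as main effects, as far as events allow. At planning rates about 152 × 0.30 + 152 × 0.15 = 68 hernias are expected, fewer once losses are removed, against 19 candidate factors, so including all of them could be unstable.
- **Complete-case result:** report it beside each analysis. In subgroups too small to impute stably, show it instead. It needs a caution: if a hernia seen at month 12 counts as observed while a hernia-free patient lost later is dropped, it overstates rates. In the simulation with 20% lost, all after month 12, it gave 0.224 for a true 0.20.

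The cost is a few sentences in the analysis plan, extra imputation runs and somewhat wider intervals. No new data are needed.

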
The hypotheses to be assessed in the primary efficacy analysis are as follows: 𝐻_0_: 𝑝_T_ = 𝑝_C_ and 𝐻_1_: 𝑝_T_ ≠ 𝑝_C_, where 𝑝_T_ and 𝑝_C_ denote the IH rates in the intervention and control groups, respectively.

The confirmatory analysis of the primary efficacy endpoint corresponds to the primary estimand defined in chapter 1.5. and will be done based on the full analysis set (FAS) according to the intention-to-treat principle. The FAS consists of all randomised patients and the patients will be considered in the group randomised to. The level of significance is set to 5% (two-sided).

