The complementary estimands will be estimated using the same primary analysis strategy as used for the primary estimand with the following differences: To estimate the first complementary estimand, the primary endpoint in the switched patients will not be taken as observed but will be imputed in the group as treated. The second complementary estimand will be estimated based on all patients treated as randomised (treatment switcher will be excluded). In the following, supplementary analyses for the primary estimand are described.

The same test as in the primary analysis will be conducted in the per-protocol set (PP, based on those patients without major protocol violation). Failure to respect the exclusion criteria or to follow the technical aspects of the assigned study group (suture material, stitch technique, used mesh) will be considered as major protocol violations. Analyses in the PP set are known to be biased and do not correspond to any estimand and thus have to be interpreted with great caution. Based on the FAS set, a complete case analysis will be performed without imputation of missing data.

All baseline variable and secondary outcomes will be evaluated descriptively, and descriptive *p-*values are reported together with 95% confidence intervals for the corresponding effects. As in the primary analysis, secondary endpoints will be assessed by a mixed regression model including the treatment group as a fixed effect and centre as a random effect. For each endpoint, relevant covariates which will be included in the analysis are pre-defined.

The safety analysis includes the calculation of frequencies and rates of complications (specific secondary outcome parameters) together with 95% confidence intervals. This analysis will be based on the safety set that contains all randomised patients in the group as treated.

All analyses will be done using SAS version 9.4 or higher.

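### One mixed regression model is assigned to every secondary endpoint; for a rare harm with no event in one arm it gives no usable between-arm effect, interval or (with Wald inference) p-value

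*Protocol article*

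**What the plan says.** In the protocol article, Statistical methods for primary and secondary outcomes {20a}, the secondary outcomes are descriptive, with p-values and 95% confidence intervals for the effects. The same kind of model as for the hernia endpoint is then prescribed: "secondary endpoints will be assessed by a mixed regression model including the treatment group as a fixed effect and centre as a random effect". Covariates for each endpoint are said to be pre-defined. The section names no estimation method, no type of test and no exception for endpoints with few events.

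The same section plans a separate safety analysis: frequencies and rates of complications with 95% confidence intervals, in all randomised patients as treated.

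Adverse event reporting and harms {22} uses six of the secondary endpoints in place of serious adverse event documentation. They include enterocutaneous fistula and revision surgery within 24 months, and haematoma within 30 days. Outcomes {12} restricts haematoma to collections that warrant surgical exploration and intervention.

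**The concern.** A maximum-likelihood logistic model, with or without a random centre effect, has no finite treatment estimate when all events fall in one arm. The harms above are the endpoints where this could happen: 152 patients per arm, spread over 10 sites (Study setting {9}) or 13 (Recruitment {15}), and severe events.

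The mesh is non-absorbable, so a harm seen only in the mesh arm is a result readers would want quantified. For such an endpoint the stated model cannot deliver the effect and interval that the plan promises. The safety analysis describes each arm but gives no between-arm comparison. A method chosen after seeing the empty arm would look data-driven.

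**Working it through.** **Denominator.** Sample size {14} assumes 30% v 15% hernia, 80% power, two-sided 5%, and then 20% loss.
- n = [1.960·√(2·0.225·0.775) + 0.842·√(0.30·0.70 + 0.15·0.85)]² / 0.15² = 120.5, so 121 per group.
- 121/0.8 = 151.25, so 152 per group and 304 in total.

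The plan's figures reproduce, and 152 per arm is used below.

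**Empty arm: 6 v 0 of 152 (illustrative).**
- Without the centre effect, log OR = ln[(6·152)/(146·0)], which is infinite. Its standard error, √(1/6 + 1/146 + 1/0 + 1/152), is infinite too.
- A program reports whatever the iteration has reached. Step 8: log OR 6.0, SE 8.1, Wald p = 0.46. Step 12: log OR 10.0, SE 59.7, p = 0.87. Step 25: log OR 23.0, SE about 39,700, p = 0.9995.
- With a random centre intercept (25-point quadrature, 10 and 13 centres, three simulated spreads of the events each), p = 0.83 to 0.96 at a loose convergence limit and 0.994 to 0.999 at tight limits. The failure therefore does not come from leaving centre out.

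**The same table by methods that tolerate a zero.**
- Fisher exact: 2·C(152,6)/C(304,6) = 0.030.
- Likelihood ratio, without centre: G = 2·[6 ln(6/152) + 146 ln(146/152) − 6 ln(6/304) − 298 ln(298/304)] = 2·(−25.27 + 29.49) = 8.44 on 1 df, p = 0.004.
- Risk difference: 6/152 − 0 = 3.9 points, Miettinen-Nurminen 95% interval 1.4 to 8.4.
- Firth-penalised logistic regression: OR 13.5 (profile 95% interval 1.6 to 1770), p = 0.013.
- For 8 v 0: Wald p about 1.00, Fisher p = 0.007.

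**No empty arm: 6 v 1.**
- log OR = ln[(6·151)/(146·1)] = 1.83; SE = √(1/6 + 1/146 + 1 + 1/151) = 1.09.
- Wald p = 0.093, Fisher p = 0.121. The model fits.

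**How often an arm is empty.** The article gives no rate for any of these harms, so the risk p is assumed equal in both arms. With q = (1 − p)^152, the chance of exactly one empty arm is 2q(1 − q).

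| Assumed risk | q | Exactly one arm empty | Both empty (q²) |
|---|---|---|---|
| 0.5% | 0.467 | 50% | 22% |
| 1% | 0.217 | 34% | 5% |
| 2% | 0.046 | 9% | 0.2% |

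**How often the table is as extreme as 6 v 0.** If the mesh tripled a control risk of 0.5%, 1% or 2%, no control event together with at least 6 mesh events would occur in about 1%, 7% and 4% of trials.

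**The case against.** Much of the opposing case stands.

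- **Test not named.** A reader might infer that p near 1 would certainly be reported. The article does not specify a Wald test, and a likelihood-ratio test of 6 v 0 gives p = 0.004. What survives any choice of test is the infinite odds ratio and the missing finite limit.
- **Rarity alone is not enough.** A reader might infer that the model fails for every rare harm. It fails when an arm is empty; 6 v 1 and 8 v 1 fit.
- **Rates not given.** A reader might take "expected to be very rare, with just a few patients each" in Sample size {14} as evidence that these harms are rare. That phrase describes two intercurrent events, re-laparotomy at the closure site and death without prior hernia. It is not a forecast for the safety endpoints.
- **Harm not hidden.** A reader might infer that a real excess would go unnoticed. The safety analysis would show 3.9% (exact 95% interval 1.5 to 8.4) v 0% (0 to 2.4). The data monitoring board sees unblinded data and reviews surgical site occurrences and major complications twice a year. No confirmatory decision rests on the descriptive p-values.
- **Limited gain in p-values.** With 1 to 5 events v 0, Fisher gives 1.00, 0.50, 0.25, 0.12 and 0.06, so an exact test would not reach 5% either.
- **Left to the analysis plan.** A sparse-data fallback often sits there, and that plan is not shown. Its absence from the article would not be a finding. The point here is that the article assigns one model to all secondary endpoints without exception.

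None of this supplies a usable between-arm effect and interval for an endpoint with an empty arm.

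**Conclusion.** The point holds in a limited form and is minor. As stated, the method gives no finite odds ratio and no two-sided interval for any binary secondary endpoint with no event in one arm. With Wald inference the p-value is also meaningless (about 1.00 against an exact 0.030 for 6 v 0).

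This rests on maximum-likelihood fitting of a logistic mixed model, which the article implies by reference to the primary analysis but does not spell out. How often it matters depends on assumed event risks: one empty arm is common at 0.5% to 1% and uncommon at 2%. The documents do not support a claim that a harm signal would be concealed, and an excess as large as 6 v 0 would itself be unusual.

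**What to change.** State in the analysis plan, before the database is closed, that a binary secondary or safety endpoint with no event in one arm, or very few in total (for example fewer than 10), is compared by the between-arm risk difference with a Miettinen-Nurminen or exact 95% interval and an exact p-value. Use Firth-penalised logistic regression if an odds ratio is wanted. Keep the mixed model for the frequent endpoints, and fix the threshold in advance.

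The cost is a sentence or two of text and a few lines of code. The sample size and trial conduct do not change. The small downside is that the sparse endpoints lose their centre adjustment.
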